# An individualized telephone-based care support program for rural family caregivers of people with dementia: study protocol for a cluster randomized controlled trial

**DOI:** 10.1186/s12877-021-02575-2

**Published:** 2021-11-04

**Keywords:** Family caregivers, People with dementia, Telephone-based, Care support, Rural area, Cluster RCT

## Abstract

**Background:**

There are about 9.5 million people with dementia in China. Up to 99% of them are cared for by their family caregivers. Family caregivers are confronted with considerable difficulties and challenges while providing care. They often experience high levels of emotional, physical, financial, and social burdens. Caregivers in rural areas experience an even higher level of burden compared to their counterparts in urban areas due to fewer health resources for dementia care. However, so far, no intervention study has been conducted to support family caregivers in rural areas of China. The aim of this proposed study is to adapt and evaluate an evidence-based and culturally-tailored individualized telephone-based care support (ITBCS) program for family caregivers of people with dementia in rural China.

**Methods:**

A cluster randomized controlled trial (RCT) will be conducted to evaluate the effectiveness of the ITBCS compared with usual care for Chinese rural family caregivers of people with dementia. A total sample of 168 rural family caregivers will be recruited. The intervention components consist of a 3-month intensive telephone-based care support intervention followed by telephone-based follow-up consultations for 6 months. The control group will receive usual care services available for them. Outcome measures include carers’ subjective burden, depressive symptoms, health-related quality of life, social support, caregiving self-efficacy, and care recipients’ difficult behaviours and competence in activities of daily living at 3, 9 and 15 months after baseline. The potential cost-effectiveness of the ITBCS compared with usual care will be assessed as well.

**Discussion:**

If effective, the ITBCS program can be adapted and used in rural areas of China as a blueprint to improve the quality of home-based care for people with dementia. Findings from the present study are significant for developing evidence-based dementia care policy in rural China.

**Trial registration:**

Chinese Clinical Trial Registry, ChiCTR2000038821, Registered 4 April 2020, http://www.chictr.org.cn/showprojen.aspx?proj=62268.

## Background

The number of people living with dementia in the world will rise to more than 131 million by 2050 [1]. It is estimated that the total global costs for dementia were US $957.56 billion in 2015. The costs will be US $2.54 trillion in 2030 [1, 2]. The average cost per people living with dementia per year (US $19,144.36) far exceeds China’s per capita disposable income [1, 2]. More than half (62%) of the total cost was attributable to the loss of formal labor from unpaid family caregivers [1–3].

Across the world, family members of people living with dementia constitute an invisible health system because they are the main source of care. This is especially true in China where dementia care services are underdeveloped, and the Chinese mainstream culture, traditional Confucianism, emphasizes that the care and support of the elderly is the responsibility of their family [4, 5]. In China, the overwhelming majority of people with dementia are cared for by family caregivers at home without external informal or formal supports [4, 5]. The availability of community and home-based support services is very limited. There are no community–based dementia care services in community health service centers. It is predicted that this situation is even worse in rural areas due to fewer health services and resources for dementia care, and more difficulties in accessing and utilizing those limited resources. Moreover, family caregivers in rural areas have poorer knowledge about dementia and feel more stigmatized than their urban counterparts [6, 7]. Close attention and concern should therefore be given to such a group in public health and health policy, and more adequate support and help need to be delivered to them [8, 9].

A body of evidence from developed countries has shown that individualized tailored support to caregivers can maintain caregivers’ mental and physical health, improve the quality of life for both care recipients and caregivers, and reduce institutionalization rates, which would have huge social and economic benefits [10, 11]. However, so far, no support intervention study has been designed or conducted for family caregivers of people with dementia in rural China. Moreover, implementing best practices in community health centers in rural areas is particularly challenging [12–14]. Firstly, there are many cases in which family caregivers have either no opportunity or no time to leave people with dementia alone at home and there are no care support groups nearby [15, 16]. Secondly, the ratio of health professionals to population is low, so delivering care support services in an individualized face-to-face manner is less possible [17, 18].

Rapid advancements in telephone technology have significantly revolutionized global connectivity. In most low- and middle- income countries, there is an increased usage of telephones with coverage of up to 90% of the population. Expansion of phone services into inaccessible and rural areas has made it a favorite means of communication [19]. In China, the latest data showed over 1.6 billion telephone lines with teledensity of 112 [20]. The widespread adoption of and people’s dependence on the telephone make it an attractive approach for delivering health-related interventions [21]. Compared to face-to-face meetings and other remote-intervention methods (e.g., internet), telephone-based interventions are advantageous because they can be easily accessible, made widely available without concern for technological barriers, are highly flexible in terms of intervention hours, and are low cost [22]. The explosive development and deep penetration of telephones make telephone-based interventions feasible in rural areas in China.

Based on a comprehensive literature review, we found that telephone-based multi-component caregiver support interventions have shown positive effects on care burden, social support, depressive symptoms, and caregiving self-efficacy of family caregivers of people with dementia [15, 23, 24]. However, evidence is limited to interventions conducted in large urban cities in developed countries. Little is known about the efficacy of telephone-based care support among families with dementia with low socioeconomic status or rural residency. Therefore, the primary purpose is to examine the efficacy of an individualized telephone-based care support (ITBCS) program on health outcomes of family caregivers and people with dementia compared to usual care in a real-world setting. This paper reports the development and study procedure of this culturally sensitive ITBCS program.

## Methods

### Study design

A cluster randomized controlled trial (RCT) design will be used to conduct the ITBCS program. The protocol was developed and guided by the SPIRIT checklist.

### Ethical considerations

The study was approved by the IRB of behavioral and nursing research in Xiang Ya School of Nursing of Central South University (Approval no. E2020141). All study-related data will be stored securely in Xiang Ya School of Nursing. All data collected during the present study will only be accessible to the researchers.

### Setting

The study will be conducted in Hanshou County of Hunan Province, Central South of China. It has a population density of 382.6 people per square kilometer. In 2018, the per capita disposable income of Hanshou County was 13,560 RMB, which was similar to the median per capita disposable income of all Chinese rural residents (13,066 RMB) [25, 26]. The ratio of health professionals in Hanshou County to population is about 1.42 per 1000, reflecting the average ratio of 1.40 per 1000 in rural China reported by WHO [27, 28]. The percentage of people aged over 60 in Hanshou County is 19.88%, which is slightly higher than the overall percentage of people aged over 60 in China (17.3%) [27, 28]. In rural areas, given the culture and traditions, older people are usually cared for by family caregivers.

### Participants

Eligible participants are defined as: 1) the primary family caregivers of a people diagnosed with dementia living at home; 2) aged 18 years or above; 3) having access to a reliable telephone; 4) having cared for people with dementia for no less than 6 months; 5) able to communicate in Mandarin, and 6) able to provide informed consent to participate in this study. The exclusion criteria for participants are: 1) hired caregivers by the family; and 2) with diseases that are unable to provide informed consent (e.g., severe mental health problems or cognitive impairment).

### Sample size

The sample size calculation for the study is based on the primary outcome, “caregiver burden score” measured by the 22-item Zarit Burden Interview (ZBI) scale, and is estimated on the basis of an earlier RCT with a telephone-based multicomponent intervention program for family caregivers of people with dementia [29]. A significant decline of 18.44 in the burden score in the intervention group at post intervention with polled standard deviation of 17.0 were reported. These values will be used to calculate the sample size in the present study. Since randomization will be conducted by community health service centers, the sample size is adjusted by the intra-class correlation coefficient (ICC) to take into account the design effect. The adjustment considered a higher ICC of 0.3 with a design effect of 3.7 for a cluster size of 10 participants in each center. To achieve at least 90% power at a 5% significance level, the required number of centers would be 7, with 70 family caregivers in each group. Assuming an attrition rate of 20%, we will need 84 participants per group or 168 in total.

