### Randomization and allocation concealment

A randomization protocol will be used to select fourteen community health service centers in Hanshou County randomly (http://stattrek.com/statistics/random-number-generator.aspx). There will be seven centers in each group (intervention group and control group). An external biostatistician who will not participate in the study intervention or data analysis will conduct the randomisation. All eligible family caregivers living in the intervention communities will be the intervention participants, while those living in the control communities will be control participants.

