### Statistical methods

All data will be double entered into an Excel database on two separate occasions and exported to SPSS software 25.0 for analysis. Internal consistency of the seven instruments will be tested using Cronbach’s alpha coefficient. For the pilot study, paired *t* tests will be conducted to evaluate whether any differences occurred in participants on the seven outcome variables pre- and post-intervention. The research team will perform all analyses of the cluster RCT study based on the intention to treat principle. Baseline data between the experimental and control group will be compared. Missing data will be imputed if deemed necessary. The most appropriate imputation methods will be decided based on the amount and pattern of missing data. A mixed effect model, which takes into account the repeated measurement of outcomes, will be conducted to analyse the primary outcome. The mixed effect model will include treatment, time, and interaction between time and treatment as the fixed effect, baseline measurement of outcome as the covariate, and subject as a random effect. The treatment difference and its 95% confidence interval (CI) will be derived from the mixed effect model. Moreover, adjusted treatment difference will be derived by adding the pre-specified covariates into the mixed effect model. All other outcomes (CES-D, SF-12, SSRS, RSCSE, NPI-Q and DAD) will be analyzed separately using this general framework.

Cost-effectiveness analyses (CEA) and cost-utility analyses (CUA) will be conducted. The difference of total costs among scenarios will first be calculated, which will be further divided by the difference in average effect sizes to estimate the incremental cost-effectiveness ratio. Inflation correction is not necessary as we will evaluate the costs covering 9 months. Multiple imputation methods will be applied to deal with the missing data in the follow-up measurements. A 95% confidence interval of the mean difference in the treatment groups’ total costs will be calculated. Cost-effectiveness acceptability curves will indicate the cost-effectiveness comparison between the ITBCS program and the usual care, with a range of different ceiling ratios presenting decision uncertainties. Furthermore, sensitivity analyses to test the robustness, such as scenarios that vary key variables will be conducted.

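### On the protocol's own inputs, 7 centres per group give about 86% power for an unadjusted two-sided test on 12 degrees of freedom, not at least 90%

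*Protocol article*

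**What the plan says.** The Sample size section of the protocol article bases the calculation on the Zarit burden score and takes its effect from an earlier telephone-intervention trial: "A significant decline of 18.44 in the burden score in the intervention group at post intervention", with a "polled standard deviation of 17.0 were reported". It then says: "These values will be used to calculate the sample size in the present study". For clustering it assumes "a higher ICC of 0.3 with a design effect of 3.7 for a cluster size of 10 participants in each center". The conclusion is "To achieve at least 90% power at a 5% significance level, the required number of centers would be 7". At 10 per centre this amounts to 70 caregivers per arm before attrition. A 20% attrition allowance raises this to 84 per group and 168 in total.

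The section on randomization and allocation concealment fixes the same number of clusters, seven centres in each of the two groups. The Statistical methods section says: "The treatment difference and its 95% confidence interval (CI) will be derived from the mixed effect model".

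The article does not name the sample-size formula, does not say whether the 5% level is one-sided or two-sided, and mentions no correction for the small number of centres.

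**The concern.** The design effect inflates the variance for clustering, but it does not allow for the fact that the between-centre variance must itself be estimated from few centres. With 7 centres per group, a valid test of treatment uses a t reference distribution with 14 - 2 = 12 degrees of freedom. Its two-sided 5% critical value is 2.179 rather than 1.960. A calculation that uses normal quantiles ignores this and overstates power.

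At stake is a design property that the article states outright. If the claim fails on its own inputs, readers are told that the chance of missing the assumed effect is at most 10% when it is higher, even if the assumed effect is accepted in full.

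**Working it through.** **Inputs.** All are from the Sample size section unless noted.
- Difference d = 18.44. It is reported as a decline in the intervention group, and is used here as the between-group difference because that is how the calculation uses it.
- Standard deviation s = 17.0.
- Intra-class correlation 0.3 and m = 10 per centre, so the design effect is 1 + (10 - 1) × 0.3 = 3.7, as stated.
- k = 7 centres per group (also in the randomization section), so 70 analysed per group.
- Level 5%. I take it as two-sided, which matches the planned 95% confidence interval.

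**Step 1: reproduce the stated figure.**
- Per-group n under individual randomisation, normal quantiles: 2 × 17.0² × (1.960 + 1.282)² / 18.44² = 17.86.
- Times the design effect: 17.86 × 3.7 = 66.1 caregivers.
- Divided by 10 per centre: 6.6 centres, rounded up to 7, which is 70 per group.
- Standard error with 7 centres: 17.0 × √(2 × 3.7 / 70) = 5.527.
- Noncentrality: 18.44 / 5.527 = 3.336.
- Normal-theory power: Φ(3.336 - 1.960) = 91.6%.

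This matches both the 7 centres and the claim of at least 90%.

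**Step 2: same inputs, between-centre degrees of freedom.**
- Degrees of freedom: 2 × (7 - 1) = 12, critical value 2.179.
- Power from the noncentral t distribution with 12 degrees of freedom and noncentrality 3.336: **86.4%**.
- A simulation of t tests on 7 versus 7 centre means (200,000 runs) also gives 86.4%.

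**Step 3: does the number per centre change the answer?**

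| Analysed per centre | Standard error | Normal-theory power | Power on 12 df |
|---|---|---|---|
| 9.6 (84 less 20%, over 7 centres) | 5.549 | 91.4% | 86.2% |
| 10 (as stated) | 5.527 | 91.6% | 86.4% |
| 12 (84 over 7 centres, no attrition) | 5.439 | 92.4% | 87.5% |

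No cluster size that the enrolment allows brings the power to 90%. At an intra-class correlation of 0.3, extra caregivers in the same centres add little.

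**The case against.** **The arithmetic is not wrong.** This stands. The design effect is correct and the 7 centres reproduce exactly under a normal approximation. What is missing is a small-sample allowance. That a normal approximation was used is an inference from the match, since the article names no formula.

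**The test might be one-sided.** A one-sided 5% test on 12 degrees of freedom gives 93.3% with 7 centres, and 6 centres give 89.0% (10 degrees of freedom), so that route also leads to 7. But nothing in the article points to a one-sided test, and the planned 95% interval points the other way.

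**The planned analysis adjusts for baseline.** This is the strongest point. The primary outcome is defined with baseline adjustment and the model carries baseline as a covariate. As an assumption, suppose baseline explains the same share of variance within and between centres. A baseline correlation of 0.35 then brings power on 12 degrees of freedom to about 90%, and 0.5 to about 94%. If baseline explains only within-centre variance, correlations of 0.5 to 0.7 give about 88% to 89%. A lower intra-class correlation would also help: at about 0.25 the unadjusted power is 90%. So the power of the adjusted analysis is unknown and may reach 90%. But the Sample size section credits neither gain, gives no baseline correlation and sets the intra-class correlation at 0.3. The 86% must therefore be labelled as the power of an unadjusted comparison.

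**The planned model has no centre effect.** The only random effect listed in the Statistical methods section is subject. A model that leaves out centres does not test treatment against between-centre variation, so it cannot support the 90% claim. It is a separate matter.

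**A reader might infer that unequal centres push power down to 80%.** The randomization section does take in all eligible caregivers in each community, so sizes could vary. With an assumed coefficient of variation of centre size of 0.3 to 0.5, power would be about 84% to 80%. But the article gives no such figure, and the Intervention section plans four field officers per centre with three caregivers each. That is 12 per centre, and 7 × 12 = 84, which matches the enrolment target. The range is a sensitivity assumption, not a property of this plan.

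**Conclusion.** The point holds in a limited form. On the stated difference, standard deviation, intra-class correlation and cluster size, 7 centres per group give 86.4% power (86.2% after the planned attrition) for an unadjusted two-sided 5% test on 12 degrees of freedom. The shortfall against 90% is 3.6 percentage points, and the type II risk is 13.6% rather than at most 10%.

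This rests on four assumptions: a two-sided 5% level, equal centre sizes, no credit for baseline adjustment, and acceptance of 18.44 as the between-group difference.

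A reader might go further and infer that the trial is seriously underpowered or must add centres. The documents do not support that. The gap is modest, and the power of the baseline-adjusted analysis cannot be computed from what the article gives. What fails is the stated figure, not the feasibility of the design.

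**What to change.** Restate the power in the Sample size section, for example: *With 7 centers per group the power is about 86% (unadjusted two-sided t test, 12 df).* This also makes the sidedness explicit.

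If the sponsor wishes to credit baseline adjustment, the assumed correlation should be stated beside the resulting power, together with whether it is taken to act within centres, between centres or both. Figures for unequal centre sizes should appear only as a sensitivity analysis, with the coefficient of variation labelled as an assumption.

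The number of centres and the 168 caregivers stay as they are. The cost is one sentence and a slightly less favourable stated power.

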The intensive ITBCS intervention consists of four steps.*Step 1 Orientation talk:* In order to address the concerns of each family caregiver during the structured care support sessions (step 3), the project field officer should have an understanding of their particular care situation. Therefore, at the beginning of the intervention, the project field officer will conduct an orientation telephone conversation with each family caregiver (lasting around 30 min). In addition, the ITBCS program process and conversation rules will be discussed. There will be four project field officers in each center and each project field officer will be assigned three family caregivers.*Step 2 Education booklet delivery:* To support the thematic introduction of each care support session (step 3), the research team will develop an education booklet summarizing information on the five support themes and listing project field officer contact details for family caregivers. This booklet could also be used as a care diary during support sessions. Each participating caregiver will receive a copy.*Step 3 Structured care support sessions:* Each family caregiver will receive five telephone-based care support sessions delivered by a project field officer. Support sessions will be scheduled to occur every 2 weeks. The duration of a support session is about 60 min. At the beginning of a support session, one of five care support themes will be introduced and discussed for around 30 min. After the thematic discussion, the remaining 30 min will be available for a discussion between the project field officer and family caregiver in order to solve individual problems within this support theme and better utilise family resources. Table 3 outlines an exemplary structure of a care support session.*Step 4 Structured evaluation of each care support session:* In the week after each care support session, a project field officer will conduct a structured telephone-based interview with each family caregiver. The semi-structured questions include the following: What was good? What did you benefit from this session? What did you miss, and do any questions remain unanswered? Which issues do you want to add to the next session?

**Table 3 Tab3:** An exemplary structure of a care support session

(1) Brief review of the previous session content and identification of any changes since then. Introduce the focus of this session and how it will be structured.	

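### Enrolling 84 per group at 20% attrition leaves about 67 caregivers, not the 70 the plan requires: the allowance equals 70 × 1.2 where 70 ÷ 0.8 is needed

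*Protocol article*

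**What the plan says.** The Sample size section of the protocol article takes its planning values from an earlier trial: "A significant decline of 18.44 in the burden score in the intervention group at post intervention", with a "polled standard deviation of 17.0 were reported". It adjusts for clustering using "a higher ICC of 0.3 with a design effect of 3.7 for a cluster size of 10 participants in each center". From these inputs it derives a requirement of 7 centers and 70 caregivers in each group.

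The next sentence adds the attrition allowance: "Assuming an attrition rate of 20%, we will need 84 participants per group or 168 in total". No inflation formula is printed.

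The total recurs in the abstract's Methods paragraph: "A total sample of 168 rural family caregivers will be recruited". The staffing described under Intensive ITBCS intervention matches it: "There will be four project field officers in each center and each project field officer will be assigned three family caregivers". That makes 4 × 3 = 12 caregivers per center, and 12 × 7 = 84.

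**The concern.** An attrition allowance should be large enough that the required number remains after the assumed loss. The required number therefore has to be divided by the expected retention, 0.80. Multiplying it by 1.20 gives a smaller figure, because the 20% loss then applies to everyone enrolled and not only to the original 70.

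At stake is whether the sample size justification is true as written. Anyone who later compares recruitment or retention with the plan would start from 70, 20%, 84 and 168. At exactly the planned attrition, the trial would miss its own evaluable number.

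**Working it through.** **Inputs, all from the Sample size section.** Difference 18.44; SD 17.0; power at least 90%; significance level 5%; ICC 0.3; 10 caregivers per center; attrition 20%. The text does not say whether the test is one- or two-sided. I assume two-sided because that reproduces the stated 7 centers (one-sided gives 6).

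**Step 1. Reproduce the 70.**

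- Without clustering: n = 2 × [17.0 × (1.960 + 1.282) / 18.44]² = 17.86, rounded up to 18 per group.
- Design effect: 1 + (10 − 1) × 0.3 = 3.7.
- With clustering: 18 × 3.7 = 66.6 per group; 66.6 / 10 = 6.66, rounded up to 7 centers; 7 × 10 = 70 per group.

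The stated requirement reproduces.

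**Step 2. Reproduce the 84.**

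- 70 × 1.20 = 84. This matches exactly.
- 70 / 0.80 = 87.5, rounded up to 88. This does not match.

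**Step 3. What 84 delivers.**

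- Completers at 20% loss: 84 × 0.80 = 67.2 per group, and 67.2 / 7 = 9.6 per center.
- Shortfall against 70: about 3 per group.
- Largest attrition that still leaves 70: 1 − 70/84 = 16.7%.

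**Step 4. What would deliver 70.**

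- 88 per group, 176 in total: 8 more than 168, and 8/168 = 4.8%.
- With equal whole centers: 10 / 0.80 = 12.5, so 13 per center, 91 per group, 182 in total.

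**Step 5. Effect on power** (normal approximation, two-sided 5%; effective n = completers / design effect).

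| Completers per group | Design effect | Effective n | Power |
|---|---|---|---|
| 70 (7 × 10) | 3.70 | 18.92 | 91.6% |
| 67.2 (7 × 9.6) | 1 + 8.6 × 0.3 = 3.58 | 18.77 | 91.4% |
| 67, design effect held at 3.7 | 3.70 | 18.11 | 90.4% |

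With an ICC of 0.3, precision depends mainly on the number of centers, so losing a few caregivers per center changes little.

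**The case against.** The strongest counter-argument is that the multiplication by 1.2 is inferred. The same 84 follows from correct division if one starts from the requirement before rounding up to whole centers: 66.6 rounded up to 67, then 67 / 0.80 = 83.75, rounded up to 84. On that route 84 enrolled leaves the 67 needed, and 70 is only a by-product of rounding 6.66 centers to 7. This is possible and cannot be excluded. But 67 appears nowhere in the article, while 70 is named as the requirement in the sentence just before the allowance, and 70 × 1.2 gives 84 with no rounding. Even on the alternative route, the printed 70, 20% and 84 remain inconsistent.

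A second argument is that little follows from the slip, and this stands. The stated aim of at least 90% power is still met with about 67 completers by the normal approximation. A t-based calculation on 12 degrees of freedom gives 86.4% at 70 and 86.2% at 67. That gap from 90% is a separate matter of few clusters, which the attrition step neither causes nor cures.

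Third, the Statistical methods section plans an intention-to-treat, repeated-measures mixed model, with imputation if needed, so caregivers who miss the last visit can still contribute. This softens the loss but does not remove it, because the primary outcome is burden at 15 months.

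Finally, the officer allocation is not a further error. It agrees with 84 and only shows that the figure has been carried forward.

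**Conclusion.** The concern holds. At the stated 20% attrition, 84 enrolled per group leaves about 67, not the stated 70. The shortfall is about 3 completers per group, equivalent to 8 enrolled caregivers overall.

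This conclusion needs only the three printed figures and no outside assumption. The power figures rest additionally on a two-sided test, equal center sizes, the normal approximation, and the article's own difference, SD and ICC; whether 18.44 is a suitable between-group difference was not examined here. On those terms the 90% target is not lost. What fails is the claim that the enrolled number provides the required one. It should be corrected, but it does not threaten the design.

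**What to change.** Correct the attrition sentence in one of three ways:

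1. Keep 168 and state that, at 20% attrition, it gives about 67 evaluable caregivers per group (9.6 per center), with the power for that number: 91.4% by the normal approximation on the plan's inputs.
2. Keep 168 and state that 84 per group allows for 16.7% attrition.
3. If 70 evaluable per group is a fixed requirement, print 88 per group and 176 in total, or 91 and 182 if every center is to enroll the same whole number. The abstract total would then change, and the allocation of 12 caregivers per intervention center would need revisiting.

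The first option is the simplest. It and the second each cost one sentence and need no extra caregivers; the third costs 8 more caregivers, or 14 more (182 − 168) with equal centers. The Trial status section puts the start of recruitment after publication, so as of the article the correction could be made before enrollment.
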